## Abstract

**Background:**

In arteriovenous graft (AVG) for haemodialysis, the primary cause of failure is venous stenosis of the graft-vein junction from neointimal hyperplasia (NIH), resulting in thrombosis. While interventions to salvage clotted AVG are known to have high clinical success rates, long-term patency rates have been suboptimal. Drug-coated balloon (DCB) has been used to treat stenosed arteriovenous access in recent years with encouraging results but data on its effect in clotted AVG is unavailable.

**Methods:**

This is an investigator-initiated, single-center, single-arm prospective pilot study to determine the safety and outcome of the sirolimus-coated balloon (SCB) in the salvage of thrombosed AVG. Twenty patients who undergo successful percutaneous thrombectomy will receive treatment with SCB at the graft vein junction. The patients will be followed-up for 6-months. The primary endpoint is the patency rates at 3-month while the secondary endpoints are the patency rates and the number of interventions needed to maintain patency at 6-month.

**Discussion:**

Unremitting efforts have been made to prolong the patency of AV accesses over the years. DCB angioplasty combines mechanical and biological treatment for vascular stenosis. Sirolimus, being a cystostatic anti-proliferative agent, has been successfully used in coronary artery interventions. As the primary pathology of vascular stenosis in the dialysis circuit is neointimal hyperplasia, the use of sirolimus in balloon angioplasty may be effective. With this prospective study, we evaluate the efficacy and safety of SCB in patients with clotted AVG.

**Trial registration:**

ClinicalTrials.gov Identifier: NCT03666208 on 11 September 2018.

## Background

In arteriovenous graft (AVG) for haemodialysis, the primary cause of failure is venous stenosis of the graft-vein junction from neointimal hyperplasia (NIH), resulting in thrombosis (Roy-Chaudhury et al. 2006). While interventions to salvage clotted AVG are known to have high clinical success rates, long-term patency rates have been suboptimal. The reported average cumulative patency rates of AVG following successful thrombolysis or mechanical thrombectomy at 3- and 6-month were 49% and 38%, respectively (Dariushnia et al. 2016). Based on this, the Society of Interventional Radiology recommended a patency threshold of 44% at 3-months and 31% at 6-month following successful thrombectomy (Dariushnia et al. 2016).

The process of neointimal hyperplasia is continuous in AVG, contributed by hemodynamic changes following anastomotic grafting, presence of the AVG itself as a foreign body provoking an inflammatory response, injury from repeated cannulations and endothelial dysfunction in the presence of uraemia (Roy-Chaudhury et al. 2006). In addition, mechanical injury during balloon angioplasty and thrombectomy may also accelerate neointimal hyperplasia. Repeated interventions are therefore often required to maintain the circuit patency of AVG.

Drug-coated balloon (DCB), a balloon catheter that delivers an anti-proliferative agent to target lesion during percutaneous angioplasty has been used to treat failing arteriovenous (AV) access in recent years with encouraging results. Paclitaxel-coated balloon (PCB) has been demonstrated in several recent randomized control trials (RCT) to be superior to plain balloon in the treatment of AV access stenosis (Irani et al. 2018; Swinnen et al. 2019; Kitrou et al. 2015; Trerotola et al. 2018). However, these trials generally have excluded patients with AVG and those with thrombosis. Whether DCB has a similar patency effect on clotted AVG is therefore unknown, necessitate the search for an answer. Sirolimus is another class of anti-proliferative agent that has low toxicity able to inhibit neointimal hyperplasia and has been successfully used in coronary artery interventions (Verheye et al. 2017). It is indicated for in-stent stenosis and small vessel disease has not been used previously in dialysis access interventions (Verheye et al. 2017; Jim et al. 2016). This study is therefore conducted to investigate the effect of sirolimus coated balloon in dialysis access interventions.

## Materials and methods

### Hypothesis, aims and design

We hypothesize that the application of SCB at the graft vein junction following successful endovascular thrombectomy minimized neointimal hyperplasia and improve AVG patency and aim to examine the efficacy and safety of SCB angioplasty of the graft vein junction following successful thrombectomy of clotted AVG.

This single-center, single-arm prospective pilot study is an investigator-initiated study that is conducted in accordance with the ethical principles that have their origin in the Declaration of Helsinki and is approved by the center’s Centralized Institutional Review Board (CIRB number: 2018/2233). Informed consent will be obtained from all subjects recruited.

### Study population

Patients with end-stage renal disease (ESRD) presenting with a thrombosed AVG since October 2018 are screened for eligibility. Eligible patients are offered participation. The potential benefits and risks of SCB are explained before informed consent is obtained from participants. A total of 20 patients will be recruited and followed up for 6 months after the intervention.

#### Inclusion criteria

Age 21–85 yearsThrombosed AVG in the armSuccessful thrombolysis of the thrombosed AVG, defined as the re-establishment of flow on Digital Subtraction Angiography (DSA) and restoration of thrill in the AVG on clinical examination

#### Exclusion criteria

Patient unable to provide informed consentPrevious bare-metal stent or stent-graft placement within the dialysis accessPresence of central vein stenosisSepsis or active infectionRecent intracranial bleed or gastrointestinal bleed within the past 12 monthsAllergy to iodinated contrast media, anti-platelet drugs, heparin or paclitaxelPregnancyLife expectancy < 12 months based on physician’s estimate

Patient who was receiving anticoagulation was initially excluded from the study. This criterion was subsequently changed to increase the potential pool of patients by allowing patients receiving anticoagulation to be enrolled in the study.

### Investigational device

The sirolimus-coated balloon (EXTREME TOUCH NEO, Concept Medical Research Private Limited, India) under investigation is coated with Sirolimus homogeneously through spray coating. The total dose of Sirolimus corresponds to 1.25 μg/mm^2^ of the surface of the balloon. The sizes of balloons available for this study are of 7 and 8 mm in diameter with a balloon length of 8 cm and shaft length of 80 cm over a 0.035″ wire.

### Study procedure

The procedure is performed according to our center protocol as previously described (Tan et al. 2019a, b) at the Interventional Nephrology Suite of a tertiary hospital in Singapore, which performs over 1000 access salvage procedures a year. After restoration of flow and adequate pre-dilatation with plain balloon, angiogram will be performed to ensure satisfactory treatment and absence of vessel recoil (defined as < 30% residual stenosis compared to the healthy segment of the AVG), SCB is then applied at the culprit lesion after appropriate sizing using the diameter of the graft (6 mm) as reference. To ensure adequate contact, the SCB balloon size is chosen in a 1:1 ratio or oversized by 1 mm the diameter compared to the reference vessel. An inflation device with a pressure gauge is used to inflate the SCB to stated burst pressure for 2 min. The size of the balloon used, inflation pressure, the transit time of the balloon, number of inflations, procedure complications (if any), and residual stenosis are recorded. Recruited patients with unsuccessful thrombectomy or unsatisfactory treatment of the graft vein junction (> 30% residual stenosis) will be considered screen failure and excluded in the study.

Post-procedure, all patients receive daily oral doses of aspirin (100 mg) and clopidogrel (75 mg) for 1 month, followed by treatment with aspirin alone for 6 months. For patients who are already on aspirin before the procedure, they will continue aspirin after the trial. For patients who are already on clopidogrel before the trial, they will continue clopidogrel after 1 month of the combination therapy. For patients who are on anti-coagulation, single anti-platelet therapy will be used for 6 months.

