### Sample size calculation and statistical analysis

The required sample size is estimated for the primary outcome variable using STATA (StataCorp.2019. Stata Statistical Software: Release 16. College Station, TX: StataCorp LLC). Based on the recommended 3-month primary patency of 44% following thrombectomy, we estimated that 3-month primary patency could improve to 75% following SCB treatment and estimated that the sample size needed is 20 subjects using an alpha risk of 0.05 and a power of 0.8.

The data analyses will be performed with STATA (StataCorp.2019. Stata Statistical Software: Release 16. College Station, TX: StataCorp LLC) and SPSS version 23 (IBM Corp, Armonk, NY). Patency rates of the AVG following SCB angioplasty will be estimated with Kaplan-Meier analysis.

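### The screen-failure rule for more than 30% residual stenosis names no time point, so read literally it can exclude patients already treated with the sirolimus-coated balloon (SCB)

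*Protocol article*

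**What the plan says.** The Study procedure section of the protocol article runs in this order:

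- After flow is restored and the lesion is pre-dilated with a plain balloon, an "angiogram will be performed to ensure satisfactory treatment and absence of vessel recoil (defined as < 30% residual stenosis" relative to the healthy graft segment).
- "SCB is then applied at the culprit lesion after appropriate sizing", and the balloon is inflated.
- Balloon size, inflation pressure, transit time, "number of inflations, procedure complications (if any), and residual stenosis are recorded".
- The next sentence covers people already recruited. It names a failed thrombectomy and then the case at issue here: "unsatisfactory treatment of the graft vein junction (> 30% residual stenosis) will be considered screen failure and excluded in the study".

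The Inclusion criteria ask only for successful thrombolysis, "defined as the re-establishment of flow on Digital Subtraction Angiography (DSA) and restoration of thrill in the AVG on clinical examination". Residual stenosis is in neither eligibility list.

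On numbers, Study population says "A total of 20 patients will be recruited and followed up for 6 months after the intervention", and the abstract's Methods paragraph says "Twenty patients who undergo successful percutaneous thrombectomy will receive treatment with SCB at the graft vein junction".

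Under Endpoints and definitions, the text after the primary safety endpoint commits to analysing adverse reactions, deaths, admissions and procedures in the six months after SCB angioplasty for the whole patient group.

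**The concern.** The exclusion is triggered by a measurement that the procedure yields at two moments, one before and one after the study treatment. The sentence does not say which is meant. It comes directly after the list of data recorded with the SCB inflation, and it applies to people already recruited.

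If the later measurement can trigger it, patients leave the analysis because of an early result of the treatment under study. Those with a poor acute result are likely to be among those who lose patency early, so the remaining group looks better than the treated group. There is no control arm in which the same selection could cancel out, and the comparison is with a fixed figure: "Based on the recommended 3-month primary patency of 44% following thrombectomy". An SCB-exposed patient, with any procedural complication, might also be left out of the one-month safety endpoint.

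**Working it through.** **1. The texts side by side.** The pre-SCB angiogram requires less than 30% residual stenosis. The post-inflation record lists residual stenosis with no threshold. The exclusion rule uses more than 30% with no time point. The eligibility lists do not tie the rule to screening, because residual stenosis is not among them. The safety commitment covers all patients, but a patient already excluded from the study may not be counted among them. The wording therefore allows both readings.

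**2. The plan's own figure.** Inputs from the sample size section: p0 = 0.44, p1 = 0.75, alpha 0.05 (sidedness not stated), power 0.8, N = 20. One-sample normal approximation, two-sided:

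n = [(1.960·√(0.44·0.56) + 0.842·√(0.75·0.25)) / 0.31]² = 18.6, so 19; with continuity correction, 22.

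The stated 20 lies between the two and is accepted. The check confirms that 44% is the benchmark the result has to beat.

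**3. Effect on the estimate.** Assumptions: 20 treated, 13 patent at 3 months, no censoring before 3 months, and two of the seven failures excluded for residual stenosis. Without censoring, the Kaplan-Meier estimate is S = x/n, and the log-log interval is S^exp(±1.96·se), with se = √[(1−S)/(nS)] / |ln S|.

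- All treated: S = 13/20 = 0.650; se = √(0.35/13)/0.431 = 0.381; interval 0.403 to 0.815. It includes 0.44.
- After exclusion: S = 13/18 = 0.722; se = √(0.278/13)/0.325 = 0.449; interval 0.456 to 0.874. It excludes 0.44.

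The shift depends on who is removed. If one of the two excluded patients had been patent, the result is 12/18 = 67%, barely different from 65%. In the other direction, if 15 of 20 treated are patent and only failures are removed, 75% becomes 15/19 = 79%, 15/18 = 83%, 15/17 = 88% or 15/16 = 94% for one to four exclusions.

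**4. Effect on a test against 44%.** The article specifies no test, so assume an exact binomial test with upper tail at most 0.025. With 20 analysed, 14 successes are needed; with 18 analysed, 13 are needed. Suppose the true rate among all 20 treated is 44% and two failures are removed.

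- If successes follow a binomial (20, 0.44), the chance of a false success goes from P(X ≥ 14) = 0.017 to P(X ≥ 13) = 0.048.
- If instead the 18 retained patients each have probability 0.44·20/18 = 0.489, it goes to 0.039.

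Either way it more than doubles and passes the 0.025 limit.

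**The case against.** The strongest reply is that the rule was meant to act before the SCB. It repeats the vocabulary and threshold of the pre-SCB angiogram. It is paired with unsuccessful thrombectomy, which can only occur before the SCB, and screen failure normally describes someone who never enters the treated group. Recruited fits consent taken before a procedure whose success decides eligibility. All of this stands, and it makes the pre-SCB reading the more likely intention. It does not make the text say so, and the article states the rule itself rather than leaving it to a fuller document.

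The numerical illustration is also constructed: two treated patients must exceed 30% after passing the pre-SCB check, both must fail, and both must be removed. That is fair. It shows how sensitive 20 patients are to the rule, not what will happen.

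A reader might go further and infer that the trial ends with fewer than 20 patients and loses power. The documents do not show this. Study population and the abstract both fit 20 patients treated and followed; a shortfall needs screen failures to count towards the 20 and not be replaced, and the article says neither. The power figures give little support either. On the exact test of step 4, power is 0.786 at n = 20, 0.717 at 18 and 0.765 at 17, so the full number is already just under 0.80, and the dip at 18 reflects discreteness. On the normal approximation the figures are 0.830, 0.785 and 0.760.

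A reader might also infer that exposed patients are definitely lost from safety. That follows only on the post-SCB reading, and the safety commitment under Endpoints and definitions points the other way.

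**Conclusion.** The concern holds as an ambiguity in a stated exclusion rule, not as a demonstrated bias. On the pre-SCB reading no treated patient is lost. On the literal post-SCB reading, the patency estimate is conditioned on a post-treatment result and conflicts with the promise to analyse events in all patients. Under the assumed two exclusions, both failures, the estimate rises by about 7 percentage points (65% to 72%) and the lower confidence limit moves from 40% to 46%, across the 44% benchmark. The article gives no exclusion rate, so the actual size is unknown and could be zero. The point is worth settling because two patients can change the conclusion and the remedy costs almost nothing. Neither a shortfall below 20 nor a loss of planned power is part of this conclusion.

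**What to change.** Amend the exclusion sentence and the statement of sample size so that:

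- for the analysis population, screen failure is decided only on the angiogram before the SCB;
- every patient in whom an SCB is inflated stays in the efficacy and safety analyses, whatever the final residual stenosis;
- the 20 are SCB-treated patients, and the number of consented but untreated patients is reported with reasons.

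This defines who is analysed and leaves clinical handling untouched. The cost is a few sentences of text. The downside is a possibly slightly lower patency estimate if any treated patient has residual stenosis, together with consenting somewhat more than 20 patients to reach 20 treated.

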### Follow-up

#### Immediate post-intervention

All participants will be followed-up after successful intervention to assess the clinical patency defined as at least one successful haemodialysis with the prescribed blood flow and immediate complications.

#### One-month follow-up

All participants will receive a call from study investigator to assess for localised infection/hematoma/bleeding of the AVG, compliance to antiplatelet therapy and identify any adverse effects from antiplatelet therapy and SCB angioplasty.

#### Three and six-month post-intervention clinic assessment

Follow-up review and assessment of AVG are performed at 3- and 6-month after the procedure. Problems with haemodialysis including difficulties with cannulation, prolong bleeding after needle removal, haematoma due to miscannulation, high venous pressure and inadequate dialysis clearance will be recorded. Ultrasound examination of the entire AVG circuit will be performed by one of the interventional nephrologists who is also the study member for any abnormalities. The minimum diameter of the graft vein junction and diameter of the adjacent healthy segment of the AVG are measured in B-mode and colour doppler mode to estimate the degree of stenosis. Three separate measurement in each mode will be obtained and the mean of these measurement will be taken as the final degree of stenosis. A significant stenosis is defined as stenosis of > 50%. At the same time, access flow is also determined from the mean of three flow measurement at the feeding brachial artery.

### Endpoints and definitions

#### Primary endpoint

The primary circuit patency rates of the AVG at 3-months following endovascular thrombectomy and SCB angioplasty

#### Secondary endpoints

The primary circuit patency rates of the AVG at 6-months following endovascular thrombectomy and SCB angioplastyThe assisted-primary and secondary circuit patency rates of the AVG at 3- and 6-months following endovascular thrombectomy and SCB angioplastyThe number of interventions needed to maintain patency in 6-months

#### Primary safety endpoint

Freedom from local or systemic adverse reaction with SCB angioplasty within the first month

The patency outcomes are classified according to the recommendations by the Society of Interventional Radiology (Gray et al. 2003). Postintervention primary patency is defined as interval following intervention until the next required intervention (angioplasty, thrombolysis or surgical revision) or time of measurement of patency. Postintervention assisted primary patency is defined as interval after intervention until subsequent access thrombosis or time of measurement of patency. Secondary patency was defined as interval after intervention until the access is abandoned or time of measurement of patency.

The study ends after post-intervention ultrasound assessment at 6-month. Patient will be considered to have completed the study if they require any intervention to the AVG or the AVG thrombosed before 6-month. Adverse reactions, deaths, hospital admissions, interventional procedure that occurred within 6-month following SCB angioplasty will be recorded and analysed for all patients. A repeat angiogram of the AVG will only be performed in patients who have not reached primary endpoints when thrombosis or problems with dialysis mentioned above occur upon assessment by patient’s primary physician.

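### Counting a patient as completed at the first graft intervention or thrombosis conflicts with secondary and assisted-primary patency, which run past that event

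*Protocol article*

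**What the plan says.** All the statements below are in the Protocol article.

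- **Completion rule** (study-end paragraph under Primary safety endpoint): "Patient will be considered to have completed the study if they require any intervention to the AVG or the AVG thrombosed before 6-month".
- **Next sentence:** "Adverse reactions, deaths, hospital admissions, interventional procedure that occurred within 6-month following SCB angioplasty will be recorded and analysed for all patients". It makes no exception for patients already counted as completed.
- **Study population:** "A total of 20 patients will be recruited and followed up for 6 months after the intervention".
- **Study end:** "The study ends after post-intervention ultrasound assessment at 6-month".
- **Primary patency:** "Postintervention primary patency is defined as interval following intervention until the next required intervention (angioplasty, thrombolysis or surgical revision) or time of measurement of patency".
- **Assisted-primary patency:** "Postintervention assisted primary patency is defined as interval after intervention until subsequent access thrombosis or time of measurement of patency".
- **Secondary patency:** "Secondary patency was defined as interval after intervention until the access is abandoned or time of measurement of patency".

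The Secondary endpoints section lists 6-month primary patency, assisted-primary and secondary patency at 3 and 6 months, and the number of interventions over 6 months. The statistical section says patency rates will be estimated by Kaplan-Meier.

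**The concern.** Of the three patency measures, only primary patency stops where the completion rule stops. A graft that has an elective angioplasty at month 2 and clots at month 4 has failed for assisted-primary patency at month 4. A graft that clots, is salvaged, and is given up at month 5 has failed for secondary patency at month 5. In both cases the deciding event comes after the patient has been counted as completed.

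The all-patient recording sentence repairs part of this. It does not name the two events that end these endpoints, thrombosis and abandonment. The article also does not say whether the 3- and 6-month visits and ultrasound go on after completion. Its Discussions section gives the ultrasound a surveillance role for aneurysm and pseudoaneurysm.

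At stake are two secondary endpoints that could look better than they are, in a pilot meant to shape a larger randomised trial.

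**Working it through.** **1. Is the primary analysis touched?** The plan's own figure is 20 patients for 44% against 75% primary patency at 3 months, alpha 0.05, power 0.8. The one-sample score formula, taken two-sided because the article does not state sidedness, gives

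n = [(1.96 × √(0.44 × 0.56) + 0.842 × √(0.75 × 0.25)) / 0.31]² = [(0.973 + 0.364) / 0.31]² = 18.6, so 19.

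This is within one patient of the stated 20. The calculation uses only 3-month primary patency, which ends at the first required intervention by definition. The completion rule removes nothing from it.

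**2. Which endpoints need data after completion?**

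| Endpoint | Ends at | Can fall after completion? | Named in the all-patient list? |
|---|---|---|---|
| Primary patency, 3 and 6 months | next required intervention | no | not needed |
| Intervention count, 6 months | month 6 | yes | yes, interventional procedures |
| Assisted-primary patency | thrombosis | yes, if the first event was non-thrombotic | no |
| Secondary patency | abandonment | yes | no |

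**3. How many patients reach the rule?** The expected number is 20 × (1 − primary patency).

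- At the hoped-for 75% at 3 months: 20 × 0.25 = 5 by 3 months. With a constant hazard, 6-month patency is 0.75² = 0.5625, so 20 × 0.4375 = 8.75, about 9 by 6 months.
- At the thresholds in the Background: 20 × 0.56 = 11.2 by 3 months (44%), and 20 × 0.69 = 13.8, about 14, by 6 months (31%). These need no hazard assumption. They do treat the thresholds as primary patency, as the sample-size section does for the 44%.

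**4. Assisted-primary patency.** A patient whose first event is thrombosis has already reached this endpoint. Only non-thrombotic first events matter. If half of first events are of that kind (an assumption), that is 4.4 to 6.9 patients.

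Let P be 6-month primary patency, with constant hazard, half of first events thrombotic, and the thrombosis rate multiplied by m after a first non-thrombotic intervention. Censoring at that intervention makes Kaplan-Meier estimate √P. The true value is √P for m = 1, P(1 − ½ ln P) for m = 2, and 2P − P^1.5 for m = 3.

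| P | Estimated | True, m = 1 | True, m = 2 | True, m = 3 |
|---|---|---|---|---|
| 0.5625 (75% at 3 months) | 75% | 75% | 72% | 70% |
| 0.31 (31% at 6 months) | 56% | 56% | 49% | 45% |

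There is no bias if risk is unchanged. If risk doubles or triples, the overstatement is 3 to 5 points in the first row and 7 to 11 in the second.

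**5. Secondary patency.** Under the rule, the only abandonment that can be seen is one at the first event. If completed patients are carried forward as patent, every later abandonment is missed and the estimate is too high. If they are censored at the first event, it is too high when abandonment is more likely after a first event than before it. The article gives no abandonment rate, so no figure is attached.

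**The case against.** The strongest reply is that completed need not mean that observation stops. It may only mean that a patient with an event is not a dropout. The very next sentence supports this reading: "interventional procedure that occurred within 6-month following SCB angioplasty will be recorded and analysed for all patients". So does the commitment to follow all 20 patients for 6 months. Most later thromboses would lead to a procedure or an admission and would be captured that way. An article also need not list every data field.

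Much of this stands. In particular, a reader might infer that the intervention count is capped at one per patient. With a constant event rate, the mean would then be 0.44 instead of 0.58 at 75% 3-month patency (24% too low), or 0.69 instead of 1.17 at 31% 6-month patency (41% too low). The arithmetic is right, but the documents do not support the inference, because procedures to 6 months are expressly recorded and analysed for everyone. Nor do they support saying that the secondary endpoints cannot be measured validly at all.

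Two things are left. A graft that clots or is given up without a procedure or admission is not covered by the list. And the favourable reading has to be inferred, because the article does not state what completion ends. The limit on repeat angiograms, to patients who have not reached primary endpoints, fits the opposite reading that study assessment stops at the first event. This is a conflict in stated text, not a detail left to a fuller document.

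It is also fair to say that no figure in the article shows risk rising after re-intervention. The Background offers only a mechanism: balloon angioplasty and thrombectomy may speed up neointimal hyperplasia.

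**Conclusion.** The point holds as an internal inconsistency that needs correcting. The completion rule stops at the first intervention or thrombosis, while secondary patency and, to a lesser degree, assisted-primary patency are defined by events that can come later and are not expressly collected.

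The bias is conditional on the completion rule being followed. It then favours the device for secondary patency, subject to the handling described in the working. For assisted-primary patency it does so only if thrombosis risk rises after a first re-intervention. About 9 to 14 of 20 patients would reach the rule by 6 months. The lower figure assumes a constant hazard, and the upper takes the 31% threshold as primary patency. The 2- and 3-fold risk multipliers and the even split of first events are illustrations, not figures from the article.

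The intervention count, both primary-patency endpoints and the sample size stand as written.

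**What to change.** Reword the study-end paragraph to say the following:

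- The first intervention or thrombosis ends only the primary-patency clock.
- In every treated patient, thrombosis, each intervention and abandonment, with dates, are ascertained to 6 months, or to death or loss to follow-up if earlier.
- The 3- and 6-month assessments already scheduled are kept after a first event.
- Assisted-primary patency is not censored at a first non-thrombotic intervention. Secondary patency is not censored at an intervention or at a thrombosis.

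This is a one-paragraph amendment. The cost is a little more data collection after the first event. The visits are already planned, and procedures are already recorded for all patients. No change to the sample size or the primary analysis is needed.
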